##### Composition of peri-implant submucosal biofilm

The Shannon diversity index will be used for expressing microbiome diversity.^
20
^ Composition of peri-implant submucosal biofilm will be analysed by means of genome analysis of bacterial samples, using an open-ended sequencing technique.^
39
^ Per implant, biofilm will be collected after supramucosal plaque has been removed by means of polishing paste (Proxyt fine paste, Ivoclar Vivadent) and a polishing cup, and the clinical crown has been rinsed with water and dried with air. Sterile paper points (Henry Schein Absorbent Points #504 medium, Henry Schein, Melville, NY, USA) and sterile dental tweezers will be used to collect intrasulcular peri-implant biofilm from four sites of each implant (mesial, distal, lingual and buccal). Samples will be transferred to tubes (Axygen Self-standing, clear, sterile Scientific Screw Cap Tubes, 2.0 ml, Axygen, Union City, CA, USA) and stored in the laboratory of ACTA at −80 °C until further analysis.

#### Covariates and confounders

The association between SB and the outcome variables described will be controlled for possible interacting and/or confounding effects from a series of other variables. These include smoking status, self-reported awake bruxism, peri-implant plaque accumulation and periodontal parameters. These variables have been chosen based on literature supporting either their purported modifying influence on the main outcomes (i.e., covariates) or their association with both our main predictor and main outcomes (i.e., confounders), and are described below.

Smoking has been shown to be associated with SB,^
40
^ peri-implant and periodontal inflammation, and bone loss.^
21
^ Also, it has been shown to affect both the composition of subgingival^
41
^ and submucosal^
42
^ biofilm. Smoking will be evaluated by four categories (never, occasional, former and current), using the questionnaire developed by Hukkinen *et al.*
^
43
^ Participants reporting smoking <5–10 packs are categorised as never-smokers. Participants having smoked >5–10 packs, but never on a regular basis, that is, daily or almost daily, are categorised as occasional smokers. Regular smoking in the past defines a participant as former smoker, whereas regular present smoking represents current smoker. Other forms of tobacco use (cigars, cigarillos or pipe tobacco) are dichotomised and defined as someone never having smoked any of these forms of tobacco (classified as never-smoker), or having ever smoked at least 50 cigars, 75 cigarillos and/or >3–5 packages of pipe tobacco (classified as current smoker).

Clenching and/or grinding of the teeth while awake are manifestations of awake bruxism^
7
^ and may form an important source of mechanical loading of implants and their suprastructures. Awake bruxism will be evaluated by a self-report 5-point scale (0=never, 1=rarely, 2=sometimes, 3=often and 4=always), using a single item derived from the Dutch translation of the Oral Behaviors Checklist.^
44
^ Subjects will be asked: ‘Could you indicate how often you have performed the following activities during the last month: clench or grind your teeth while you are awake?’.

Peri-implant supramucosal biofilm has reported to be crucial for the development of peri-implant disease.^
6
^ Per implant, plaque accumulation is scored according to the modified Plaque Index^
39
^ as follows:

- Score 0: no detection of plaque;- Score 1: plaque only recognised by running a periodontal probe across the smooth marginal surface of the implant. Implants covered by titanium spray in this area always score 1;- Score 2: plaque can be seen by the naked eye;- Score 3: abundance of soft matter.

Periodontal parameters of all present natural elements and implants, with the exception of the implants being studied, will be recorded, as periodontal disease has been reported to favour the occurrence of pathology around dental implants.^
45
^ These parameters include the number of clinical pockets with probing depths of ⩾5 mm and Bleeding Index. Probing depths are measured as the distance from the gingival (or mucosal) margin to the bottom of the deepest clinical pocket on six sides of the examined tooth or implant (mesio-buccal, mesio-lingual, disto-buccal, disto-lingual, buccal and lingual), using a standardised periodontal probe (Click-Probe 3/5/7/10 blue, KerrHave) with pressure of 0.2–0.25 N. Pockets with depths of ⩾5 mm are scored as either present or absent. Bleeding on probing is assessed on the same sides described above, using a standardised periodontal probe (Click-Probe 3/5/7/10 blue, KerrHave) with gentle pressure of 0.2–0.25 N as either present or absent within 30 s after probing. The Bleeding Index (%) is calculated using the formula: (number of sites with bleeding/total number of sites examined)×100.

Morphological and restorative aspects of the implant treatments are registered in the dental record of each subject as part of regular clinical practices of ACTA, and will serve for the description of the baseline characteristics of our subjects’ implants. These include the number of occluding pairs of natural teeth, geometrical characteristics of the implants, factors related to loading of the implants, prosthetic characteristics of the implant-supported suprastructures and the status of their antagonists.

The number of occluding pairs of natural teeth is defined as the number of pairs between upper and lower equivalent natural teeth, by oral assessment. Implant characteristics recorded are the type of implant (manufacturer and system) and implant size (diameter and length, in mm). Characteristics related to loading of the implants and loadability of the receiving bone site include time of loading the implant with the definitive prosthesis (immediate, i.e., within 1 week after implant placement; early, i.e., between 1 week and 2 months; or late, i.e., after 2 months), bone or soft tissue augmentation procedures, bone quality (according to the criteria proposed by Lekholm and Zarb^
46
^), and position of implant (within arch, lower or upper jaw). Prosthetic characteristics of the implant-supported suprastructures are noted. Type of abutment (material, fabrication method), type of implant-supported suprastructure (single crown, fixed partial denture with or without cantilever), retention type (cemented or screw-retained) and material of the suprastructure are registered. Regarding the antagonists of the studied implants, the structure of opposing occlusal contact(s) (natural tooth, implant or none), type of restorative material present on opposing supporting cusp(s), and occlusal contact of implant-supported restoration with antagonists during maximum intercuspation protrusion and/or laterotrusions are registered after oral assessment, with the aid of a 12 μm occlusal foil (Hanel occlusion foil 12 μm, Coltene, Langenau, Germany).

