**Materials and Methods::**

Our study is a single-centre, double-blind, prospective cohort study with a follow-up time of 2 years. Ninety-eight participants fulfilling inclusion criteria (planned treatment with implant-supported fixed suprastructure(s) and age 18 years or older) will be included. Sleep bruxism will be monitored at several time points as masticatory muscle activity during sleep by means of a portable single-channel electromyographic device. Our main outcomes are biological complications (i.e., related to peri-implant bleeding, probing depth, marginal bone height, quality of submucosal biofilm and loss of osseointegration) and technical complications (i.e., suprastructure, abutment, implant body or other).

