### Participants

Participants will be enrolled in the study if they fulfil the inclusion and exclusion criteria, agree to participate, and sign the informed consent form. Participants will be recruited from the clinic of the Department of Oral Implantology and Prosthetic Dentistry of the ACTA. This department treats patients situated in the greater Amsterdam area. Inclusion criteria are: a planned treatment with implant-supported fixed suprastructure(s) and age 18 years or older. Exclusion criteria are: opposing teeth of implant-supported fixed suprastructure(s) are restored with removable artificial teeth; patients categorised in the classes 3 or higher according to the American Society of Anesthesiologists (ASA) system for classification of physical status;^
31
^ use of an occlusal splint, mandibular repositioning appliance or any other bruxism mitigating device during sleep; active periodontitis at the time of implant placement; known allergy to the EMG device electrode material; usage of a pacemaker; and swollen, infected or inflamed tissues or skin eruptions, e.g., phlebitis, varicose veins etc. in the placement area of the EMG device electrode. Pregnant women will not be treated with dental implants. Pregnancy after the placement of implants will not be a reason to stop participation of the subject in the study.

All patients of the clinic of Oral Implantology and Prosthetic Dentistry for which one or more implants are planned will be screened for fulfilment of the inclusion and exclusion criteria and willingness to participate in a clinical study. Eligible patients will be thoroughly informed about the study, upon which they will be given 1-week time to consider participation. Written informed consent will be obtained prior to enrolment of a patient in the study. Participation is voluntary and can be withdrawn at any time, without consequences for the course of treatment.

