### Sample size

To analyse the association between predictors and outcome variables for both our main aim and our secondary aim, multilevel regression analyses will be used.^
32
^ Therefore, we will use the suggested formula ‘50+8*k* (*k*; number of predictors)’ for the calculation of our sample size.^
33
^ On the basis of that formula, this study (with six predictors) will need a minimum sample size of ‘50+48=98’ participants.

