The raw EMG data will be analysed for the calculation of SB outcomes upon completion of the entire follow-up period of the study, using a stepwise analysis tool incorporated in the BruxismDetector software. This software has been developed at the Department of Oral Kinesiology of ACTA. The beginning of the sleep period will be defined as 30 min after electrode placement, and the end at moment when the EMG signal starts to exhibit an unstable pattern prior to electrode removal. During total sleep time, EMG amplitudes >20% of the highest maximum voluntary clenche will be selected for SB episode scoring, according to the Lavigne *et al.*
^
10
^ criteria. Type of SB episodes will be scored as follows: phasic (at least three suprathreshold EMG bursts lasting ⩾0.25 and <2.00 s, and separated by two interburst intervals of <2.00 s), tonic (one EMG burst lasting⩾2.00 s) or mixed (both phasic and tonic types of bursts). When the time interval between two bursts is ⩾2.00 s, a new episode is considered to start.^
10
^ Per recording, two SB outcome variables will be derived, viz., the number of bruxism episodes per hour of sleep (Epi h^−1^), and the bruxism time index (i.e., the total time spent bruxing divided by the total sleep time, times 100%).^
9,36
^

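### The named adjustment variables, which appear to fill the six predictors behind N = 98, include neither age nor sex, so the sleep bruxism estimates are open to confounding by both

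*Protocol article*

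**What the plan says.** All places are in the protocol article.

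- **Covariates and confounders** says that the association of SB with the outcomes will be controlled for a series of other variables: "These include smoking status, self-reported awake bruxism, peri-implant plaque accumulation and periodontal parameters". It gives a reason for the choice: "These variables have been chosen based on literature supporting either their purported modifying influence on the main outcomes", or association with both the main predictor and the main outcomes.
- The same section specifies the periodontal parameters: "These parameters include the number of clinical pockets with probing depths of" 5 mm or more, and the Bleeding Index. It assigns morphological and restorative aspects of the implant treatment to baseline description only.
- **Sample size** takes 50 + 8k, with k as the "number of predictors)’ for the calculation of our sample size", and concludes that "this study (with six predictors) will need a minimum sample size of" 98. It does not list the six.
- **Participants** admits anyone of "age 18 years or older" with a planned implant-supported fixed suprastructure. There is no upper age limit and no matching.
- **Single/multiple analysis** tests SB in Cox models (technical complications, loss of osseointegration) and linear models (bleeding, pocket depth, bone height, microbiome diversity). These are then expanded with confounders and covariates.
- **Table 1** lists smoking status, awake bruxism, plaque and periodontal parameters at baseline. Age and sex appear in no row.

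**The concern.** The result for each outcome is the coefficient for SB, and in a cohort that coefficient is only as good as its adjustment. The article sets its own test for a confounder, association with both predictor and outcomes, and applies it to smoking, awake bruxism, plaque and periodontal status. It gives no reason for leaving out age and sex, although the cohort spans all adults. The limitations in the Discussion do not mention it either.

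Suppose age or sex is linked to SB level and also to bone height, probing depth, bleeding, technical complications or biofilm diversity by a route that does not run through the variables already in the model. The SB coefficient for that outcome then absorbs part of the age or sex effect. Since the direction is unknown, both a spurious risk factor and a masked one are possible.

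The sample size adds to the difficulty. If the named variables already use up the six predictors, 98 leaves no room for more terms under the rule the protocol chose.

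**Working it through.** **1. The plan's own figure.** N = 50 + 8k with k = 6 gives 50 + 48 = 98. This matches the Sample size section and the abstract ("Ninety-eight participants fulfilling inclusion criteria").

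**2. Which six?** The document does not itemise them. Two counts of the named variables give six:

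- SB as one measure per model, smoking, awake bruxism, plaque, pockets of 5 mm or more, Bleeding Index: 6.
- Both SB measures ("Per recording, two SB outcome variables will be derived"), smoking, awake bruxism, plaque, periodontal parameters as one group: 6.

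Either way the named variables use all six places, and age and sex are not among them. Both counts give smoking a single term, although it has four categories.

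**3. The same rule with age and sex added, one term each.**

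| Predictors | k | 50 + 8k |
|---|---|---|
| As planned | 6 | 98 |
| Plus age or sex | 7 | 106 |
| Plus age and sex | 8 | 114 |
| Plus age and sex, smoking as 3 terms | 10 | 130 |

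With both added, the rule asks for 114 − 98 = 16 more participants than planned.

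**4. When does omission cause bias?** Put SB, age (A) and the outcome (Y) on a standardised scale, given the other covariates: Y = b·SB + g·A + error, with correlation r between SB and A. Leaving A out makes the SB coefficient estimate b + r·g, so the bias is r × g. The documents give neither r nor g. Over an assumed range of 0 to 0.3 for each:

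| r | g = 0 | g = 0.1 | g = 0.2 | g = 0.3 |
|---|---|---|---|---|
| 0 | 0 | 0 | 0 | 0 |
| 0.1 | 0 | 0.01 | 0.02 | 0.03 |
| 0.2 | 0 | 0.02 | 0.04 | 0.06 |
| 0.3 | 0 | 0.03 | 0.06 | 0.09 |

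A simulation of 400,000 observations with b = 0 agrees: the unadjusted SB coefficient is 0.0 at r = 0.3, g = 0; 0.09 at r = 0.3, g = 0.3; and 0.002 at r = 0, g = 0.3. Both links are needed for bias.

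**5. What that does to a test (linear model, one observation per participant).** Take a standard error of about 1/√90 = 0.105.

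- *False positives.* A bias of 0.09 is 0.09/0.105 ≈ 0.85 standard errors. The rejection rate of a two-sided 5% test is then Φ(−1.96 + 0.85) + Φ(−1.96 − 0.85) ≈ 13.7%. At a bias of 0.01 it is 5.1%, and at 0 it is 5%.
- *Lost power.* By Fisher's z with n = 98, a true correlation of 0.28 has atanh(0.28) × √95 ≈ 2.80, so power is Φ(2.80 − 1.96) ≈ 80%. An opposing bias of 0.04 leaves 0.24 and about 66%. An opposing bias of 0.09 leaves 0.19 and about 47%.

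These figures illustrate scale only. They do not cover the Cox models or the clustering of implants within participants.

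**The case against.** The strongest reply has four parts.

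**The list may not be closed.** It opens with an inclusive phrase, the six predictors are never itemised, and no sentence bars further terms. This stands: a reader might infer that the plan forbids adjustment for age or sex, but the text does not say so. What remains is that the article names specific variables, gives the grounds for choosing them, shows the same ones at baseline in Table 1, and sizes the study on a count they appear to fill.

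**A condensed article need not carry everything.** Demographics could sit in the full protocol or analysis plan, and Table 1 is a visit schedule. That would be decisive if the article deferred the choice of covariates. It does not: it states and justifies a set and ties N to a predictor count. Table 1 also holds self-reported smoking and awake bruxism, so it is not limited to clinical measurements, though it could still omit fixed characteristics. Its silence is supporting evidence only.

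**The document contains no evidence of confounding.** This also stands. No passage links age or sex to SB or to any outcome, so every magnitude above is assumed. A reader might infer that any age or sex difference in SB is counted as an SB effect in every model. That is wrong: with no effect on the outcome given the other covariates, the bias is zero, and the outcomes need not share an age or sex effect.

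**Adding terms conflicts with the sample size rule.** Under that rule, 98 is too few for eight predictors. This is correct and belongs in the cost of the change.

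**Conclusion.** The point holds in a conditional form. The named adjustment variables include neither age nor sex, and with SB they appear to account for the six predictors behind N = 98. In a non-randomised cohort of all adults, this leaves the SB estimate for an outcome confounded if age or sex relates both to SB and to that outcome after the other covariates. The direction cannot be told from the document.

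The size rests wholly on assumption: 0 to 0.09 SD of outcome per SD of SB for r and g between 0 and 0.3. At the upper end, a 5% test would reject falsely about 13.7% of the time, or 80% power would fall to about 47%. At the lower end nothing changes. The document supports neither the claim that every model is biased nor the claim that adjustment for age and sex is ruled out. The change is still worth making, because it bears on the main inference and costs little.

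**What to change.** - **Covariates and confounders:** add age (continuous) and sex to the named list.
- **Single/multiple analysis:** state that both enter the adjusted Cox and linear models.
- **Table 1:** enter both in the baseline row.
- **Sample size:** itemise the predictors and restate k as 8. Say that the rule gives 50 + 64 = 114, that enrolment stays at 98, and that 98 is therefore below the rule-of-thumb minimum for the fully adjusted model.

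**Cost.** Two more coefficients per model. In a linear model with one term per predictor and one observation per participant, residual degrees of freedom go from 98 − 7 = 91 to 98 − 9 = 89, a loss of about 2%. The Cox models come under more strain if events are few, and the document gives no expected number of events for this cohort. The stated minimum is no longer met by the protocol's own rule and this has to be acknowledged, but that rule is not a power calculation and the shortfall does not by itself require more enrolment. Age has to be known to check eligibility. The document does not say where sex is recorded (a reader might assume the dental record), so its collection should be stated.

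### The other-tobacco rule codes lifetime cigar, cigarillo or pipe use as current smoking, against the protocol's own timing-based smoking definitions, and leaves light users without a class

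*Protocol article*

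**What the plan says.** All the relevant text is in the protocol article under Covariates and confounders. Smoking is one of the adjustment variables: "These include smoking status, self-reported awake bruxism, peri-implant plaque accumulation and periodontal parameters". The section gives a reason for including it, beginning "Smoking has been shown to be associated with SB", and goes on to link smoking to peri-implant and periodontal inflammation, bone loss and biofilm composition.

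The scale is set as "Smoking will be evaluated by four categories (never, occasional, former and current"). The main rule, expressed in packs, then fills the four categories:

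- Never: "Participants reporting smoking <5–10 packs are categorised as never-smokers".
- Occasional: "Participants having smoked >5–10 packs, but never on a regular basis, that is, daily or almost daily, are categorised as occasional smokers".
- Former and current: "Regular smoking in the past defines a participant as former smoker, whereas regular present smoking represents current smoker".

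A separate sentence covers cigars, cigarillos and pipe tobacco and splits their use in two. The lower class is "someone never having smoked any of these forms of tobacco (classified as never-smoker"). The upper class is "having ever smoked at least 50 cigars, 75 cigarillos and/or >3–5 packages of pipe tobacco (classified as current smoker").

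Table 1 schedules smoking status at baseline and at 12 months. The section Single/multiple analysis says the regression models will be expanded to examine confounders and covariates.

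**The concern.** The same label, current smoker, has two meanings. In the pack-based rule it requires regular smoking now. In the other-tobacco rule it requires only that a lifetime amount was once reached. Someone who stopped cigars decades ago would share a category with a daily cigarette smoker.

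This matters because the study is an observational cohort, so the sleep bruxism (SB) estimate depends on adjustment. Of the variables listed in this section, smoking is the one for which the text expressly states an association with SB, and it is also linked there to the biological and biofilm outcomes. Mis-coding it can leave some confounding in the adjusted SB estimate.

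**Working it through.** No planning figure is at issue, so the check sets the two rules side by side. Inputs are the definitions quoted above. For each other-tobacco history, the class under the printed other-tobacco rule is compared with the class that the pack-based timing definitions would give. Cigars serve as the example; any one of the three product amounts is enough for the upper class.

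| Cigar history (no other product at or above its amount) | Other-tobacco rule as printed | Timing definitions applied to the same history | Result |
|---|---|---|---|
| None | never | never | agree |
| 1–49 cigars | no class | never (below the amount) | gap |
| 50 or more, regular in the past, stopped | current | former | conflict |
| 50 or more, never regular | current | occasional | conflict |
| 50 or more, regular now | current | current | agree |

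Two of the five histories are assigned wrongly and one is not assigned at all. Both conflicts follow from the wording under any reading, because the upper class has no condition on present use or on regularity.

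The gap arises because the lower class requires no use whatever, while the upper class starts at the stated amounts. The pack-based rule has no such gap, since its never class includes people with a little use.

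**Repeat assessment.** A lifetime total cannot fall. A participant coded current at baseline through cigars, cigarillos or pipe is therefore still coded current at 12 months, even after quitting. A regular cigarette smoker who quits between the two assessments moves to former.

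**Size.** Those mis-coded as current are people at or above an other-tobacco amount who do not now smoke any product regularly. A cigar or pipe user who is also a regular cigarette smoker now, or who still uses cigars or pipe regularly, is coded correctly. The document gives no prevalence for smoking or for cigar, cigarillo or pipe use, so the count is unknown. Each affected participant is 1/98 ≈ 1.0% of the planned cohort.

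**The case against.** The strongest reply is that the problem is narrow. It reaches only some cigar, cigarillo and pipe users, possibly very few of 98, and it concerns one of several adjustment variables. The questionnaire is cited but not shown and may already record present use. A full protocol or analysis plan could also set out how the product-specific answers combine into one variable, and an article may leave that out. The gap at 1–49 cigars has an obvious answer by analogy with the pack-based never class. All of this stands as a limit on severity. It does not remove the conflict: the article prints an explicit rule that turns ever into current, and a fuller document could correct it only by contradicting it.

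Two stronger readings are tempting, and the document does not support them.

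- A reader might infer that everyone without other-tobacco use becomes a never-smoker, including daily cigarette smokers. The sentence is limited to other forms of tobacco, and nothing says its label replaces the cigarette class. Read as a product-specific class, it causes no conflict.
- A reader might infer a large loss of confounding control. Supposing 20 true current smokers and 5, 10 or 15 mis-coded ex-users, their share of the current group would be 5/25 = 20%, 10/30 = 33% or 15/35 = 43%. None of these counts comes from the document. The smoking contrast would shrink by those shares only if ex-users carried exactly never-smoker risk. The loss of confounding control would further depend on how smoking relates to SB and to each outcome within the model.

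**Conclusion.** Wrong as written; minor. The other-tobacco rule assigns current smoker on lifetime amount alone, which contradicts the same section's definitions of former, occasional and current, and it leaves users below the amounts without a class. Followed literally, it mis-codes past and irregular cigar, cigarillo and pipe users in every smoking-adjusted model and hides their quitting at 12 months. Neither the number affected nor the size or direction of any effect on the SB estimate can be derived from the document. The conclusion rests only on the printed definitions and needs no assumption about prevalence.

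**What to change.** Use the stated cigar, cigarillo and pipe amounts only as the cut-off between never and ever use, and then apply the existing cigarette definitions to these products, in this order:

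1. Below the amount: never.
2. At or above the amount, but never regular: occasional.
3. At or above the amount, regular in the past but not now: former. This includes people whose use is now only irregular.
4. At or above the amount, regular now: current.

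Applied in this order, every history gets exactly one class, the 1–49 cigar group falls in never, and the 12-month assessment can record quitting. Add one sentence saying that a never label for other tobacco does not replace the participant's cigarette class. The cigarette rule itself stays unchanged.

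The cost is a change in derivation wording. If the questionnaire does not already record present and regular use of other tobacco, it also needs at most one added question at the baseline and 12-month smoking assessments.
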